### Provisions for post-trial care {30}

Participants enrolled in the study are covered by the business liability insurance of the BG University Hospital Bergmannsheil for negligent harm during the perioperative period including study-related procedures like blood collection. This will cover the additional health care and compensations for damages by claims pursued through the courts.

All respirators in the study are CE-marked and dispose about additional insurance that covers direct harm in association with the correct use of these medical devices.

### Outcomes {12}

#### Primary outcome of the main study

As the primary outcome mean final values of IL-8 plasma concentration 6 h after CPB termination will be assayed by enzyme-linked immunosorbent assay (ELISA).

Previous studies in cardiac surgery could demonstrate lower postoperative plasmatic IL-8 concentrations after protective low tidal volume ventilation and/or higher PEEP level administration [21, 22]. In a sub-study of the PROVHILO trial in non-cardiac surgery, postoperative plasmatic IL-8 concentrations were higher in the group that developed PPCs [23]. Moreover, IL-8 is one of the key cytokines in LIRI [8, 24] and recent data suggest IL-8 levels to be associated with an increased risk of 28-day mortality in patients with acute respiratory distress syndrome in a panel of 6 biomarkers [25]. In this first large clinical trial of individualized FCV, IL-8 plasma concentrations function as a surrogate biomarker for the specific objective and hypothesis of the proposed project.

#### Important secondary outcomes of the main study

Oxygenation indices at different perioperative time points (Table 1, “art BGA”)Plasma IL-8 concentrations at different perioperative time points (Table 1)Perioperative ventilation pressures (mean and peak airway pressure, driving pressure), C_dyn_, airway resistances, and mechanical power of ventilation [26] up to 24 h after termination of CPBWeaning times from mechanical ventilationIncidence of postoperative pneumonias with the need of antibiotic treatment during the complete inpatient stay (suspected and/or confirmed, see below)Incidence of postoperative pulmonary complications (PPCs) during the first seven postoperative days including compound outcome analysis and single PPC analysis. PPCs encompass (modified from [20])New invasive ventilationNon-invasive ventilationPost-extubation respiratory acidosis (pH ≤ 7.3 and PaCO2 > 45 mmHg)ReintubationReadmission to ICU due to pulmonary reasonsMild hypoxemia defined as an PaO2/FiO2 < 300 but ≥ 200Moderate hypoxemia defined as an PaO2/FiO2 < 200 but ≥ 100Severe hypoxemia defined as an PaO2/FiO2 < 100Acute respiratory distress syndrome (ARDS) according to the Berlin criteria [27]Implantation of a veno-venous ECMOSuspected pneumonia defined as new pulmonary infiltrates plus 2 or more of the following clinical parameters: temperature > 38.5 or < 35.5°C, leucocyte count > 12 or < 4/nl and purulent secretions including antibiotic treatmentConfirmed pneumonia defined as pulmonary infiltrates and microbiological germ proof of tracheal aspirationsBronchoscopyPleural drainage due to pleural effusionsPleural drainage due to pneumothoraxIncidence of postoperative extra-pulmonary complications (PEPCs) during the first seven postoperative days including compound outcome and single PEPCs analysis. As PEPCs the following items are definedSepsis and septic shock (as defined in [28])Postoperative coronary interventionPostoperative wound infection with the need for antibiotic treatmentOther sites of infection with the need for antibiotic treatmentPericardial tamponade or other bleeding with intervention such as re-sternotomyImplantation of any device for extracorporeal life support (ECMO, Impella) or intra-aortic balloon pumpNon-pulmonary ICU readmissionAcute kidney injury with a Kidney Disease: Improving Global Outcomes (KDIGO) stage 2 or 3 [29]Postoperative delirium diagnosed by the Confusion Assessment Method for the ICU (CAM-ICU) [30]Systemic inflammatory response syndrome (SIRS) (according to [28]) free days during the first seven postoperative daysLengths of intensive/intermediate care unit stays and time to dischargeHospital readmission and mortality rate after one and 6 months post-surgery (Table 1, phone surveys)

Regarding the more patient-relevant secondary endpoints of FLOWVENTIN HEARTSURG with respect to both PPCs and PEPCs, these were validated as primary (composite) endpoints in large multicenter ventilation trials of the past decade [9, 11–13, 17].

#### Outcome parameters for ancillary studies

Sub-study on cardiovascular-ventilation interactions (n≥40/group)Perioperative echocardiographic evaluation of pulmonary circulation and right ventricular function parameters at three different times, (1) preoperative TTE before induction of anesthesia (baseline), (2) TEE 1 before CPB, and (3) TEE 2 30 to 60 min after CPB (Table 1). Parameters include [31]iPulmonary acceleration time and estimated pulmonary artery pressures during ins- and expirationiiRight ventricular index of myocardial performance (RIMP)iiiTricuspid annulus velocity S’ivTricuspid annular plane systolic excursion (TAPSE)vRight ventricular outflow tract fractional shortening (RVOT FS)viFractional area change (FAC)viiLongitudinal strain analyses by speckle tracking echocardiography.For explorative analyses, final values of each right function parameter
at the defined times as well as the relative changes from baseline to
intraoperative data and relative changes between pre- and post-CPB measurements
will be assessed.Serum concentrations of CK-MB and high-sensitivity troponin up to postoperative day 5 (Table 1)Plasmatic brain natriuretic peptide (BNP) concentrations and relative changes from baseline (i.e. before induction of general anesthesia) up to postoperative day 5 (Table 1)Central venous oxygen saturations at 8 perioperative time points up to 24 h after CPB (venous BGA, Table 1)Perioperative catecholamine concentrations up to 24 h after CPB (Table 1)Sub-study on perioperative lung aeration parameters based on electrical impedance tomography (EIT) data (n≥50/group)Parameters include [32]iGlobal inhomogeneity indexiiCenter of ventilationiiiRegional ventilation delayivSurface of ventilated areavDorsal fraction of ventilated area [33].

EIT recordings are performed at 6 perioperative times: (1) patient breathing spontaneously in supine position before induction of general anesthesia (baseline), (2) after individualization of preoperative, group-specific ventilation, (3) after postoperative ICU admission and re-individualization of group-specific ventilation, (4) on pressure support ventilation with a PEEP of 5–6 cm H_2_O and support pressure of 6 cm H_2_O during weaning from mechanical ventilation, (5) 30–60 min after extubation, (6) 24 h after CPB end (Table 1). The explorative analyses will include final values of each parameter as well as relative changes from baseline, i.e., the spontaneously breathing patient preoperatively.

**Table 1 Tab1:**
[figure not shown]
Time schedule for enrolment, allocation, interventions and assessments in the main and ancillary studies. Calculations for the Assess Respiratory Risk in Surgical Patients in Catalonia (ARISCAT) Score [34] can only be completed when SpO_2_ is measured at the time of patient arrival in the induction room. The EuroSCORE II [35] is recalculated after CPB based on the actual intraoperative cardiac surgical interventions. Additional arterial BGAs are conducted simultaneously to the EIT recordings on CPAP and pressure support ventilation during weaning as well as 30–60 min after extubation. Close-out of participants is after the second phone survey 6 months after the cardiac surgery procedure. The first phone survey is conducted one month postoperatively. Post-allocation time points: Base, patient breathing spontaneously before induction of anesthesia; T−2, after group-specific individualization of ventilation and before skin incision; T−1, 15 min after thoracotomy; T0, after CPB termination and transfusion stop from the extracorporeal circulation; T1–24, appropriate hour after CPB end. BGA, blood gas analysis; BNP, brain natriuretic peptide; CK-MB, creatine kinase MB; CPAP, continuous positive airway pressure ventilation during weaning; PEEP, positive end-expiratory pressure; PEPCs, postoperative extra-pulmonary complications; POD, postoperative day; PPCs, postoperative pulmonary complications

### Participant timeline {13}

The participant timeline is shown in Table 1.

### Sample size {14}

The sample size was calculated according to the study hypothesis. Based on the previous results of protective ventilation protocols in the setting of on-pump cardiac surgery [21, 22], the effect size of the intervention on postoperative plasmatic IL-8 concentrations was estimated as moderate being well aware about the exploratory nature of this study of mid-term clinical FCV utilization. Under these assumptions (Cohen’s d = 0.5), the total sample size required to achieve a power of 1-β = 0.8 for a two-sample *t*-test at a two-sided level α = 0.05 resulted in 2*64 = 128 [36]. As the primary endpoint is obtained 6 h after termination of CPB, most dropouts will be due to a second cardiopulmonary bypass phase within this time frame or other in {11d} defined stop criteria in estimated 10% or less of the cases. Therefore, an additional 10% of patients will be randomized summing up to a total sample size of 128*1.1 = 140.8 ≈ 140 randomized study participants.

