### Trial design {8}

FLOWVENTIN HEARTSURG is designed as a randomized, controlled, single-center, superiority trial with two parallel groups. The group assignment will be performed by block randomization with an 1:1 allocation.

In different ancillary studies, the effect of FCV versus PCV on perioperative lung aeration based on EIT-derived data as well as right ventricular, echocardiographic function parameters will be investigated following an exploratory approach.

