### Plans to promote participant retention and complete follow-up {18b}

Patients are allowed to withdraw study participation at any time and for any reason. However, as interventions are only applied when the patient is under general anesthesia and most study data are collected within the first 24 h after CPB while the patient is being either under general anesthesia or shortly after awakening from an open chest cardiac surgery procedure, withdrawal rate taking together with the dropout rate (see {14}) and missing data is thought to be less than 10% of the cases during the whole study period.

In order to reduce the risk of loss to follow-up during phone surveys up to 6 months post-surgery, at least one phone number of a close relative is recorded at the time of recruitment.

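### The 140 randomised patients keep the required 128 evaluable only for losses up to 8.6%, not up to the 10% that the allowance is meant to cover (minor)

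*Protocol article*

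**What the plan says.** Sample size {14} of the protocol article takes a standardised difference of 0.5 and a two-sample t-test. It gives "the total sample size required to achieve a power of 1-β = 0.8" "at a two-sided level α = 0.05 resulted in 2*64 = 128".

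The same section attributes most expected losses to a second bypass run or other "defined stop criteria in estimated 10% or less of the cases". It then inflates: "an additional 10% of patients will be randomized summing up to a total sample size of 128*1.1 = 140.8", and rounds this to 140. The abstract shows these as 70 per group, in line with the "block randomization with an 1:1 allocation" in Trial design {8}.

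The retention section {18b} takes withdrawals, dropouts and missing values together: "missing data is thought to be less than 10% of the cases during the whole study period".

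The section on non-adherence and missing data {20c} removes patients who meet a stop criterion from the analysis and omits missing values. It expects almost no missing values for the primary endpoint.

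**The concern.** A 10% loss is a share of the patients randomised, whereas the plan adds 10% of the patients needed at the end. The two bases differ, and the second gives too small a number. Rounding 140.8 down rather than up takes off a little more. The allowance is therefore 12 patients, while 10% of 140 is 14.

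The losses do reduce the analysed number. Under {20c} stop-criteria patients and missing values drop out of the primary analysis, and the intention-to-treat principle stated there does not bring them back.

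What is at stake is the consistency of a figure that the main report is likely to repeat. The chain from 128 through 10% to 140 does not close, because 140 × 0.9 is not 128. The effect on power is slight.

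**Working it through.** **Inputs.** d = 0.5, two-sided α = 0.05, power 0.80, two-sample t-test, 128 evaluable, losses of at most 10%, 140 randomised (all from {14}); 1:1 allocation ({8}).

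**1. The plan's evaluable number.** The noncentral t calculation gives n = 63.77 per arm, so 64 per arm and 2 × 64 = 128. Power at 64 per arm is 0.8015. The plan's figure is reproduced.

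**2. The plan's inflation.** 128 × 1.1 = 140.8. This is also reproduced, but it rounds up to 141; the plan takes 140.

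**3. Inflation that covers a 10% loss.** N × (1 − 0.10) ≥ 128, so N ≥ 128/0.9 = 142.2. That is 143, or 144 as 2 × 72, which is 3 or 4 more than 140. Rounding up to 141 would not have been enough, since 141 × 0.9 = 126.9.

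**4. The loss that 140 can absorb.** 140 − 128 = 12 patients, and 12/140 = 8.57%.

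**5. Power across the range of losses** (d = 0.5, two-sided 0.05, losses split about evenly between arms):

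| Loss from 140 | Evaluable | t-test power |
|---|---|---|
| 5% | 133 | 81.6% |
| 8% | 128.8 | 80.4% |
| 12 patients (8.57%) | 128 | 80.1% |
| 13 patients (9.3%) | 127 | 79.8% |
| 14 patients (10%) | 126 | 79.5% |

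At 63 per arm, the difference detectable with 80% power is d = 0.503 instead of 0.500.

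**6. Possible effect of the covariate.** The primary analysis in {20a} is a linear regression with EuroSCORE II, not the t-test used for sizing. The documents give no correlation between EuroSCORE II and IL-8, so the values here are assumptions. Replacing d by d/√(1 − r²) at 63 per arm gives power of 79.9% for r = 0.10, 80.2% for r = 0.13 and 81.1% for r = 0.20.

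**The case against.** The strongest reply is that nothing material is lost, and most of it stands.

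- **The 10% is a ceiling.** Both {14} and {18b} word it as an upper limit, and no section states 10% as the expected loss. Read strictly, the retention section's wording allows at most 13 losses, leaving 127. A reader might infer that the trial will end with 126 evaluable patients; the documents do not support that. From 0 to 12 losses the full 128 are there.
- **Power is hardly touched.** A reader might also infer that the stated 80% power is not delivered. At the worst case within the protocol's own range it is 79.5%, which is 0.8 to the precision that the plan uses. A normal approximation asks for only 63 per arm, and 126/0.9 is exactly 140. A modest correlation with EuroSCORE II would also close the gap.
- **The printed sum is correct.** 128 × 1.1 is 140.8, and the rule of adding 10% is stated openly.
- **Lack of slack is no defect.** Any design inflated exactly to its assumed loss has none beyond that loss, including one based on 128/0.9.

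What does not fall is the narrow point. The plan states 128, not 126, as its requirement. It sizes the allowance from losses of up to 10%, and the allowance protects 128 only up to 8.6%. Between 8.6% and 10%, which the protocol itself treats as possible, its own target is missed by one or two patients. The covariate argument cannot settle this, because {14} does not rely on it and no correlation is given.

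**Conclusion.** Wrong as written, and minor. By the plan's own inputs, covering a loss of up to 10% takes 143 randomised patients (144 for equal arms), and 140 does so only up to 8.6%. At the upper bound the shortfall is two evaluable patients, about 0.6 percentage points of unadjusted power against 64 per arm (79.5% against 80.1%), and 0.003 in detectable d.

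This rests on the t-test of {14} at d = 0.5, on losses falling about evenly between the arms, and on {20c} removing those patients from the analysis. It does not show that the trial is underpowered or that a 10% loss is to be expected.

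**What to change.** Keep 140 and restate the last sentence of Sample size {14}, for example:

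> With 140 patients randomised, 128 remain evaluable for losses of up to 8.6% (12 patients). At the upper bound of 10%, 126 remain (63 per arm) and the power of the unadjusted t-test at d = 0.5 is about 79.5%.

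The wording should not turn 10% into the expected loss. The cost is one sentence in the protocol and its repetition in the main report. No extra patients are needed, and conduct and analysis stay as they are, so the change is feasible even though recruitment was planned to end in November 2022 (Trial status). The only price is a slightly less favourable power figure at the upper bound.

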### Recruitment {15}

As most patients are accompanied for 12–14 h during the perioperative period by the same anesthesiologist for protocol adherence only one participant per day is generally feasible. Depending on this availability, preoperative patients will be screened for eligibility criteria on the day before surgery.

In order to motivate for trial participation, all suitable patients are informed about the possibly improved perioperative medical care, not only by the intervention but especially during the postoperative period when being supervised by an extra medical doctor in the ICU. However, medical treatment except of interventions is at the discretion of the respective anesthesiologist or intensive care physician in charge. Generally, recruitment is performed in an informative way with plenty of time to answer all questions and encounter individual concerns. Additionally, every patient is made aware of the option to cancel the study participation at any time without any effect on further medical treatment except of interventions.

## Assignment of interventions: allocation

### Sequence generation {16a}

Randomization to the control (PCV) or intervention (FCV) group is performed by a computer-generated schedule with an 1:1 allocation using permuted blocks of lengths 4 and 6 in order to ensure sufficient concealment.

### Concealment mechanism {16b}

The online-based software REDCap® will only release the randomization code to group-specific intervention assignments after entering sex and age as well as the affirmation of inclusion and negating exclusion criteria of a recruited patient. Assignment is only performed if the participant`s time slot for the procedure is confirmed by the respective OR manager.

### Implementation {16c}

The allocation sequence was generated by independent staff from the Department of Medical Informatics, Biometry & Epidemiology, Ruhr-University Bochum. Patient recruitment and enrolment is organized and executed by trained personnel from the Department of Anesthesiology, Intensive Care and Pain Medicine, BG University Hospital Bergmannsheil. Finally, interventions are assigned only by the principal investigator (SB) using the online-based software REDCap® with no access to the allocation sequence.

## Assignment of interventions: blinding

### Who will be blinded {17a}

Due to application of interventions with different respirators and ventilatory equipment, care providers and assessors cannot be blinded during group-specific mechanical ventilation in FLOWVENTIN HEARTSURG. However, trial participants are blinded at any time point until individual trial close-out after 6 months post-surgery.

As soon as the patients are extubated, blinding of at least study assessors is possible. At the earliest, this can be achieved 6 h after CPB as most patients are in the process of weaning or already extubated. At the latest from 24 h after CPB onwards, all involved study assessors are masked as well as data analysts at a later time. Blinding of these parties is not lifted before a fixed data set of each outcome parameter is created.

### Procedure for unblinding if needed {17b}

Not applicable as per default care providers and assessors are not blinded until the intervention withdrawal—which is when patients are eventually weaned and extubated during the postoperative care or after 24 h of group-specific ventilation post CPB.

### Plans for assessment and collection of outcomes {18a}

#### Primary and secondary outcomes of the main study

For the analysis of plasmatic IL-8 concentrations 6 h after CPB (primary study endpoint), central venous blood will be collected under aseptic conditions from a central venous catheter in 4.0 ml EDTA tubes. Consequent laboratory processing is initiated within 50 min after collection and includes centrifugation of full blood at 2000 g for 10 min and freezing of 200 μl aliquots at − 80 °C. All assessors have been specifically trained for this basic laboratory work. One aliquot per participant will be analyzed in duplicate by an ultrasensitive IL-8 Human ELISA Kit, according to the manufacturer’s instructions (Thermo Fisher Scientific, Darmstadt, Germany). ELISA plates will be occupied with aliquots starting with the most recent and ending with the very first patient in order to diminish inter-assay variability. ELISA assessments are conducted only by one single specialized laboratory staff member unknown to the group assignment in order to further decrease inter-observer variability and to promote the reliability of the ELISA results.

For the collection of main secondary outcomes like oxygenation indices, ventilatory parameters, PPCs and PEPCs, participants are accompanied continuously from in- to extubation and are visited on postoperative days 1, 3, 5, and 7. All assessors are physicians with a special training for maximum inter-rater reliability.

#### Ancillary studies

*Perioperative cardiovascular-ventilation interactions:* The assessors of right ventricular function parameters by preoperative TTE and intraoperative TEE are senior anesthesiologists in cardiac anesthesia with a special diploma in these diagnostic procedures. Assessments are conducted at distinctly defined times ({12} and Table 1).*Perioperative lung aeration parameters based on EIT data:* EIT raw data are recorded on six serial perioperative times ({12} and Table 1) with a patient-matching EIT-belt positioned between the 4^th^ and 6^th^ intercostal space. EIT parameters will be analyzed by a trained and blinded assessor with the matlab tool EITdiag and PC-version of PulmoVista® (Draeger Medical GmbH, Lübeck, Germany).

A trial-specific case report form (CRF) for the collection of data for the main and ancillary studies can be found in additional file 1.

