**Fig. 1 Fig1:**
[figure not shown]
Left column: Course of airway pressures, airway gas flows and ventilated volume during ins- and expiration with conventional PCV (from top to bottom). The relatively abrupt change of airway pressures at the beginning of both ins- and expiration causes a rapid acceleration of airflows into or out of the lungs. The remaining flow profiles during ins- and expiration are characterized by flow deceleration (mid-inspiration and mid-expiration) and eventually end-inspiratory and end-expiratory no-flow phases. Right column: The constant and continuous airway flows during ins- and expiration in FCV (top diagram) effect a linear increase of airway pressures, which are measured in the trachea or at the conventional tube tip when using a conventional tube adapter in FCV (middle). Consequently, ventilated lung volume also increases and decreases linearly during ins- and expiration (bottom)

Since 2017 flow-controlled ventilation (FCV) has been commercially available as a new ventilatory mode (EVONE®, Ventinova Medical B.V., Eindhoven, the Netherlands). With continuous low and constant gas flows during entire ins- and expiration, FCV is the only mode of ventilation in which expiration can be controlled (Fig. 1). This approach reduces mechanical power and dissipated energy of FCV to a minimum in invasive ventilation [3]. In large animal experiments, the application of FCV improved lung function, lung recruitment, homogeneity of ventilation, and reduced lung tissue inflammation in a model of acute respiratory distress syndrome compared to conventional ventilatory modes [4, 5]. Regarding the clinical short-term application of FCV in interventional cross-over studies in lung healthy [6] and obese patients [7], lung function with respect to oxygenation and decarboxylation capacities and regional ventilation distribution were improved compared to conventional volume-controlled ventilation. However, no clinical data exist about the mid-term utilization of FCV in a perioperative context, let alone larger randomized-controlled clinical trials (RCTs). Additionally, even if the theoretical considerations and mathematical models attribute a reduction of mechanical power to FCV [3, 4], clinical data are lacking.

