#### Secondary driving pressure (DP) trial in the FCV group

In the FCV group, an additional incremental DP trial in 1 cm H_2_O steps is initiated after the PEEP trial. This trial evaluates if the V_t_ increases over-proportional to the C_dyn_ on the previous DP level when the DP is increased by 1 cm H_2_O. As soon as the increase of V_t_ is just proportional, lower, and/or a respiratory rate of 5/min is reached, the DP trial is terminated. In the FCV group patients are ventilated with a DP consistent with the highest C_dyn_ ± 1–2 cm H_2_O during the pre- and intraoperative period [4] (Fig. 2). This approach favors a liberal V_t_ and focuses on a reduction of the respiratory rate and airway flows in order to minimize mechanical power [4].

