### Confidentiality {27}

After trial enrolment, every patient receives a pseudonym consisting of letters and serial numbers. From then onwards, personal as well as study-related data will only be collected under this pseudonym in the patient’s individual paper CRF. The list of personal patient data linked to the specific pseudonym will be locked in a separate cabinet with access only by the principal investigator.

Echocardiographic data will be anonymized before data analysis and EIT data will be saved under the corresponding pseudonym (see additional file 1, page 9). For phone surveys after 1 and 6 months, the assessor will receive a list with the patient names including date of birth for a correct identification. However, obtained data of these surveys will again be collected in the corresponding pseudonymized CRF (see Additional file 1, page 14).

In general, all study-related information will be stored securely at the study site and any personal patient information will be either locked in cabinets with limited access or will be only accessible via specific user names and passwords in digital databases.

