Additionally, the study protocol includes the evaluation of perioperative lung aeration by electrical impedance tomography (EIT) embedded in an independent ancillary study of FLOWVENTIN HEARTSURG. EIT is a relatively new technique that allows for non-invasive point-of-care, two-dimensional visualization of air movements within the thoracic cavity without exposure to radiation. This allows for repetitive real-time assessments but implies a far lower resolution compared to current computed tomography analysis. EIT measurements can be performed on spontaneously breathing and mechanically ventilated patients which is the case in the study protocol. Half of the perioperative EIT recordings are under spontaneous breathing conditions (preoperative baseline and postoperatively after extubation as well as 24 h after CPB end) whereas the other half under invasive ventilation (after individualization of group-specific ventilatory settings preoperatively, after postoperative ICU admission and on pressure support ventilation during respiratory weaning). A similar perioperative approach of EIT measurements as in this study protocol has been recently published as a substudy of the PROVECS trial [33]. However, the authors focused on the results of only two EIT-derived parameters (dorsal fraction of ventilation and regional lung compliance) at four different time points up to the second postoperative day. The current study protocol comprises 5 numerical EIT-derived indices at 6 perioperative time points. With this approach, we hope not only to shed light on the effect of the interventions but also the course of respiratory “milestones” on the way through a cardiac surgery procedure and the subsequent intensive care period.

Regarding the echocardiographic evaluation of right ventricular function and pulmonary circulation, the respective substudy represents a nearly complete set of systolic right ventricular function parameters as described in the most recent guidelines for cardiac chamber quantification by echocardiography in adults by the American Society of Echocardiography and the European Association of Cardiovascular Imaging in 2015 [31].

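### The EIT reader is called blinded without qualification, but blinding cannot be assured for recordings 2 and 3 and is not protected for recordings 1, 4, 5 and 6

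*Protocol article*

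**What the plan says.** - **Reader.** The protocol article, section {18a}, Ancillary studies, states: "EIT parameters will be analyzed by a trained and blinded assessor with the matlab tool EITdiag". The PC version of PulmoVista is named as a second tool. No recording is excepted.
- **Recordings on the allocated mode.** In the outcome section {12}, ancillary studies, two of the six recordings are listed as "2) after individualization of preoperative, group-specific ventilation, (3) after postoperative ICU admission and re-individualization of group-specific ventilation".
- **Other recordings.** The fourth is "4) on pressure support ventilation with a PEEP of 5–6 cm H_2_O and support pressure of 6 cm H_2_O during weaning", given once without distinction by arm. The Discussion adds: "Half of the perioperative EIT recordings are under spontaneous breathing conditions". These are recording 1 (baseline), recording 5 (after extubation) and recording 6 (24 h after bypass).
- **What differs between the arms.** The Fig. 1 legend says that in FCV "ventilated lung volume also increases and decreases linearly during ins- and expiration". For PCV it describes decelerating flow with phases of no flow at the end of inspiration and of expiration. The section on the driving pressure trial describes a liberal tidal volume and a reduced rate in FCV; one of its stopping conditions reads "a respiratory rate of 5/min is reached, the DP trial is terminated". The section on the PEEP trial holds PCV at 6–8 ml/kg predicted body weight.
- **File labels.** Section {27}, Confidentiality, says "EIT data will be saved under the corresponding pseudonym". The same sentence says that echocardiographic data are anonymized before analysis; no such step is stated for EIT.
- **General blinding.** Section {17a} says that care providers and assessors cannot be blinded while group-specific ventilation runs. It also says that assessors and data analysts are masked later, and that this is kept until a fixed data set exists for each outcome.

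**The concern.** Blinding an offline reader normally means withholding the allocation code. That works only if the material itself does not show the allocation. Here the treatment is a pattern of air movement, and EIT records air movement, so in recordings 2 and 3 the measured signal is itself a likely carrier of the arm.

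The remaining recordings could be read under real masking, and the later ones (4, 5 and 6) are made when the patient is no longer on the allocated mode. If the reader has already learned the arm from recording 2 or 3 under the same pseudonym, that masking may be lost.

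The investigators also hold a directional expectation. Section {20b} anticipates better dorsal ventilation distribution with FCV in obese patients, and the dorsal fraction of ventilated area is one of the listed EIT parameters. An expectation combined with knowledge of the arm is the situation that blinded reading is meant to prevent. What is at stake is the accuracy of a blinding claim and the credibility of the EIT comparisons reported under it.

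**Working it through.** The plan gives no figure for this point, so the check sets the sections side by side and then counts recordings.

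**Step 1. Which recordings can show the arm by their content?**

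| Recording | Condition (section {12}; Discussion) | Difference between arms described in the article |
|---|---|---|
| 1 | Spontaneous breathing, before induction | None |
| 2 | Allocated ventilation, preoperative | Volume curve, tidal volume, rate |
| 3 | Allocated ventilation, ICU | Volume curve, tidal volume, rate |
| 4 | Pressure support, one setting stated | None |
| 5 | Spontaneous breathing, after extubation | None |
| 6 | Spontaneous breathing, 24 h after bypass | None |

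**Step 2. Would an EIT reader see the difference?** The Discussion describes EIT as a real-time, two-dimensional picture of air moving in the chest. One of the listed parameters, regional ventilation delay, is by its name a timing measure. A linear rise and fall of volume in one arm, against a decelerating pattern with pauses in the other, should therefore be visible in a tracing over time. The protocol does not say so outright. It is a strong inference from the Fig. 1 legend, the driving pressure section and the Discussion.

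**Step 3. Can the arm pass from recordings 2 and 3 to the others?** Files are saved under one pseudonym per patient, so a reader working from files so labelled can tell that six recordings belong together. Section {12} also plans relative changes from baseline, so the recordings must be linked at some stage. The article does not say whether files are recoded before reading, in what order they are read, or whether a patient's six files are seen together. Carry-over is therefore possible but not established.

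**Step 4. Count at the stated minimum size (at least 50 per group).**

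- Patients: 2 × 50 = 100.
- Recordings: 100 × 6 = 600.
- On allocated ventilation (2 and 3): 100 × 2 = 200, and 200/600 = one third.
- Remaining (1, 4, 5 and 6): 100 × 4 = 400, exposed only if linked to recording 2 or 3 of the same patient before or during reading.

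**The case against.** **Storage is not reading.** The Confidentiality section says how files are stored, and the pseudonym itself does not encode the arm. Recoding and reading order are details that an article may leave to the full protocol. This stands in part: the missing detail is not itself a fault. The unqualified claim of a blinded reader is on the page, however, and for recordings 2 and 3 no recoding would make it true.

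**The limit is already conceded.** Section {17a} says that assessors cannot be blinded during group-specific ventilation. That can be read as meaning bedside staff, with {18a} meaning an offline reader, so the two sections are in tension rather than in flat contradiction. On either reading {18a} remains unqualified.

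**The scope for bias is undocumented.** The outputs are five numerical indices computed with software, and the article does not describe what the reader chooses. This stands, and it limits the weight of the point. A trained human assessor is named, though, so full automation is not stated either.

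**Stronger readings that the document does not support.**

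- A reader might infer that blinding fails for every recording of a patient. The shared pseudonym permits this but does not prove it, and four of the six recordings carry no described sign of the mode.
- A reader might infer that respiratory rate alone separates the arms. The article gives neither a minute volume nor an achieved FCV tidal volume. Both arms start at 6–8 ml/kg, the driving pressure trial can stop early, and 5/min is one stopping condition rather than a set rate. A calculation with assumed, non-overlapping tidal volumes would build in its own result.
- A reader might infer that the later recordings are meant to show a benefit lasting beyond ventilation. No section gives them that role.

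**Conclusion.** The point holds in this limited form. Blinding cannot be assured for recordings 2 and 3, which are one third of all recordings (200 of 600 at minimum size). For recordings 1, 4, 5 and 6 (400 of 600) blinding is achievable, but nothing in the article protects it.

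This rests on two assumptions: that EIT tracings show the differences the protocol describes between the modes, and that patients follow the usual sequence given in the Discussion. Section {11a} allows group-specific ventilation for up to 24 h after bypass, so for a few patients the later recordings may not fit the table above.

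The consequence is minor. The EIT work is an exploratory ancillary study, and the primary endpoint is untouched because its ELISA is run by one laboratory member unaware of assignment. The size or direction of any reader bias cannot be computed from the document. The point is still worth acting on, because the claim is broader than the design supports and is cheap to correct.

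**What to change.** 1. Give every EIT recording its own random code before reading, with the key held by data management rather than the reader.
2. Read recordings 1, 4, 5 and 6 of all patients in shuffled order, and lock the results before any recording 2 or 3 is opened.
3. Analyse recordings 2 and 3 on a segment fixed in advance by rule, for example a set time window after individualization, so that the reader makes no selection.
4. Link recordings within a patient for change from baseline only after reading is complete. The planned analysis is unchanged.
5. Amend {18a}, and the later report, to say that recordings 1, 4, 5 and 6 are read blind and that 2 and 3 are not.

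The cost is some file handling, reading in two batches, and a narrower blinding claim. Because reading is offline, no extra patient procedure or staff is needed. If some files have already been read, the report should say which ones and in what order.
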